## Abstract

**Aim:**

Intermittent fasting, a dietary intervention of alternate eating and fasting, has gained popularity in people trying to lose weight. Intermittent fasting could provide an alternative to classic caloric restriction in people with type 2 diabetes mellitus. The aim of the study is to determine the impact of a 12‐week intermittent fasting regimen compared with usual care in people with type 2 diabetes mellitus receiving insulin therapy.

**Methods:**

This open, single‐centre, randomized controlled trial investigates participants with type 2 diabetes mellitus on insulin therapy and a glycated haemoglobin A1c (HbA1c) of ≥53 mmol/mol (≥7.0%) and a minimum insulin dose of 0.3 IU/kg body weight per day. Participants are randomized in a 1:1 ratio to either 12 weeks of intermittent fasting or the standard care group. All participants receive dietary counselling, continuous glucose monitoring, measurement of the resting metabolic rate, an oral glucose tolerance test, body composition measurement via dual‐energy X‐ray absorptiometry and stool samples for microbiome analyses at the beginning and at the end of the intervention. Two co‐primary outcomes (analysed in hierarchical order) were chosen for the study: (i) the difference in the change of HbA1c from baseline to 12 weeks and (ii) the difference in the number of participants achieving a combined end point encompassing a body weight reduction of at least 2%, an insulin dose reduction of at least 10% and an absolute HbA1c reduction of at least 3 mmol/mol (0.3%) between the two groups.

What’s new
Blood sugar control and weight management can be challenging for people with type 2 diabetes mellitus.Intermittent fasting has become a popular option to manage weight, improve fasting glucose and insulin sensitivity.This study will investigate the feasibility and efficacy of intermittent fasting in people with insulin‐treated type 2 diabetes mellitus.The information gained will enhance our understanding of fasting interventions, which can be used to improve clinical dietary recommendations.

## INTRODUCTION

1

Diabetes mellitus is characterized by chronic hyperglycaemia and impaired carbohydrate, lipid and protein metabolism caused by complete or partial insufficiency of insulin secretion and/or insulin action.^1^

Reduction of body weight has been a key strategy in mitigating the risk of developing diabetes.^2^ Among obese and people with prediabetes, a weight loss of 5%–7% improves fasting glucose and insulin sensitivity.^3^, ^4^ The most commonly used approach for weight loss is daily caloric restriction. In recent years, intermittent fasting has become a prominent approach because it consists of only a restricted food intake on either specific days of the week or during a predefined period of the day.

A subtype of intermittent fasting, alternate day fasting comprises food restriction and normal food consumption on a day‐to‐day alternating basis, has been shown to reduce body weight by 8% in obese people after 3–24 weeks of treatment. Additionally, a reduction in triglycerides, low‐density lipoprotein (LDL) cholesterol, systolic blood pressure and insulin resistance has been documented.^5^, ^6^, ^7^, ^8^

When comparing caloric restriction to intermittent fasting dietary regimens in humans, both dietary regimens achieve reductions in visceral fat mass, fasting insulin and insulin resistance in overweight and obese people.^9^

So far, available human data of intermittent fasting focusing specifically on people with type 2 diabetes mellitus treated with insulin, looking into potential glycaemic, body weight and treatment improvements, are mainly limited to case series.^10^, ^11^

Moreover, fasting and feeding schedule may interfere with the circadian rhythm and hence sleep length and quality^12^ and in addition, poor sleep has been associated with insufficient glycaemic control.^13^ The majority of the available data on intermittent fasting and sleep derives from Ramadan studies and were inconclusive with regard to sleep duration and sleepiness of people.^14^

People with type 2 diabetes mellitus have a distinct gut microbiome and disturbed diversity compared with healthy controls, shown to be able to affect and modulate lipogenesis, fat storage and metabolism^15^, ^16^, ^17^, ^18^, ^19^, ^20^ While dietary interventions are supposed to affect microbiome composition, research data on the effects of intermittent fasting on the microbiome in people with type 2 diabetes mellitus and insulin therapy is scarce and required.^21^, ^22^

The aim of the current study is to investigate safety and efficacy of intermittent fasting in people with type 2 diabetes mellitus and insulin therapy compared with usual care.

## MATERIALS AND METHODS

2

### Study design

2.1

This was an open, single‐centre, parallel, two‐arm, randomized controlled trial to evaluate the effect of intermittent fasting on participants with insulin‐treated type 2 diabetes mellitus over a period of 12 weeks. The investigations were performed at the Medical University of Graz, Division of Endocrinology and Diabetology, Interdisciplinary Metabolic Medicine Trials Unit. The protocol was approved by the Ethics Committee of the Medical University of Graz (EK 30‐350 ex 17/18). All participants gave written consent prior to any study‐related procedure. This study was conducted according to the principles of the Declaration of Helsinki, GCP‐ICH and the protocol and the requirements of the concerned regulatory authorities.

### Inclusion and exclusion criteria

2.2

The study population consists of participants with type 2 diabetes mellitus, aged between 18 and 75 years (both inclusive) and a glycated haemoglobin A1c of ≥7.0% (≥53 mmol/mol). Main inclusion criteria: total daily insulin dose ≥0.3 units per kilogram of body weight and stable bodyweight in the preceding 3 months (change in weight <±3 kg). Participants who are willing to comply with study procedures, attend the study site, participate in the necessary protocols and comply with fasting protocols are included in the study. Main exclusion criteria contain active, known malignancies within the last year (excluding intraepithelial neoplasia of prostate, gastrointestinal tract and basalioma), pregnancy or intention of becoming pregnant, breastfeeding, a history of any chronic disease process that could interfere with interpretation of study results, new hormonal supplementation or contraceptive hormonal medication changes in the last 2 months, type 1 diabetes mellitus or other forms of diabetes mellitus, an acute or chronic inflammatory disorder, alcohol abuse with more than 15 standard drinks per week, overnight shifts or intake of illicit substances.

### Sample size estimation

2.3

Sample size was estimated using the parameters of a previously published randomized controlled trial^23^ that investigated the effects of intermittent fasting on glycaemic control in people with type 2 diabetes mellitus. We based our sample size estimation on the baseline HbA1c data of this study 66 ± 7 mmol/mol (8.2 ± 0.6%) and estimated that a sample size of 23 participants in each group will have a power of 85% to detect a clinically important mean difference of 6 ± 7 mmol/mol (0.5 ± 0.6%) in HbA1c between the groups at a two‐sided alpha error of 5%. For the co‐primary outcome a sample size of 20 participants in each group would provide a power of 0.80 to detect a difference in proportion of 40% between the intermittent fasting and the control group. This calculation assumes 10% of the control group will reach the co‐primary end point (combined end point encompassing a body weight reduction of at least 2%, an insulin dose reduction of at least 10% and an absolute HbA1c reduction of at least 3 mmol/mol [0.3%]).

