**FIGURE 1 dme14813-fig-0001:**
[figure not shown]
Flow chart of the intervention (an optional single follow‐up after 1 year will be added)

46 participants (23 per group) with insulin‐treated type 2 diabetes mellitus are randomly assigned to ‘intermittent fasting’ or ‘control group’, in a 1:1 ratio. Intermittent fasting comprises 3 days (Monday, Wednesday, Friday) of 75% caloric restriction (i.e. only 25% of the recommended calorie intake; this intake is only allowed as breakfast and/or lunch to maintain an 18 hours period of fasting) and 4 days (Tuesday, Thursday, Saturday and Sunday) of 0% caloric restriction (i.e. ad libitum calorie intake) in 1 week.

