#### Statistical assessment

2.8.19

We defined two primary outcomes for the study to capture both changes in glucose control and the change of glucose control in conjunction with the insulin dose and the body weight changes. We will analyse these two primary end points in a hierarchical order, where the difference in the change of HbA1c from baseline to week 12 between the study groups is analysed first (at a significance level of 0.05). If the null hypothesis of this primary outcome (i.e. there is no difference in the change of HbA1c from baseline to week 12 between the two study groups) is rejected, the second primary outcome (i.e. the difference in the number of participants achieving a combined end point encompassing a body weight reduction of at least 2%, an insulin dose reduction of at least 10% and an absolute HbA1c reduction of at least 3 mmol/mol [0.3%]) will be tested at a significance level of 0.05. As the analysis will be performed in hierarchical order, according to the European Medical Agency (EMA) guideline on multiplicity issues in clinical trials (section 5.1.2.) no reduction or splitting of the α level is required.^35^

For the primary analysis of the primary outcomes, we will perform an intention‐to‐treat (ITT) analysis of all participants randomized using an unpaired t‐test for the change in HbA1c (alpha = 5%), followed by a chi‐square test comparing the two proportions of the co‐primary outcome (alpha = 5%), if the first test rejects the null hypothesis.

We will then perform sensitivity analyses for the primary outcomes using multivariate imputation by chained equations) for missing data in the ITT cohort. Additional sensitivity analyses will be performed in the per protocol cohort (people adherent to the intervention according to section 2.8.19) without and with data imputation for missing data.

Furthermore, analysis of covariance or multiple linear regression model adjusting for baseline HbA1c and multiple logistic regression model adjusting for baseline co‐primary, respectively, will be performed using the ITT population.

Finally, we will perform linear mixed‐effect models without multiplicity adjustment and generalized linear mixed models, respectively, for the primary outcomes in the ITT population.

Continuous secondary outcomes will be analysed using both unpaired t‐test and linear mixed‐effect models.

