#### Study status

2.8.23

First participant visit was 16 September 2019. As of 22 December 2021, we have recruited 46 participants (100%).

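### HbA1c power: 23 per group are both calculated and randomised, with no allowance for loss, and the printed inputs give about 0.79 to 0.81 rather than 85% even with complete follow-up

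*Protocol article*

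**What the plan says.** All references are to the protocol article.

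- **Section 2.3, Sample size estimation.** For HbA1c, the investigators "estimated that a sample size of 23 participants in each group will have a power of 85" per cent for a "mean difference of 6 ± 7 mmol/mol (0.5 ± 0.6%) in HbA1c between the groups", "at a two‐sided alpha error of 5" per cent. For the composite, 20 per group is said to give 0.80 power for a 40-point difference from a control rate of 10%. No attrition rate and no inflation for loss appear.
- **Section 2.8, text with Figure 1.** The number randomised is "46 participants (23 per group) with" insulin-treated type 2 diabetes.
- **Section 2.8.23, Study status.** The article reports that "we have recruited 46 participants (100" per cent), so 46 was the full target.
- **Section 2.8.19, Statistical assessment.** The primary analysis of HbA1c is an unpaired t-test in the intention-to-treat population. Multiple imputation "for missing data in the ITT cohort" is listed among the sensitivity analyses. The composite is tested only if the HbA1c test rejects.

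**The concern.** The calculated, randomised and recruited numbers are identical, so every participant without a week-12 HbA1c takes the primary test below its planned size. Imputation is placed in the sensitivity analyses. On a plain reading, such a participant contributes nothing to the primary t-test.

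HbA1c is also the gate to the composite, so lost HbA1c power reduces the chance of any confirmatory claim. A non-significant result would be read against a stated 85%, when the design gives less on its own printed inputs and less again after any loss.

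**Working it through.** **Inputs.** Section 2.3 gives a two-sided alpha of 0.05, 23 per group, a difference of 6 with SD 7 mmol/mol, and the same pair as 0.5 with SD 0.6%. Section 2.5 gives 1:1 allocation. Section 2.8.19 gives the unpaired t-test.

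**Formula.** Standardised difference d = difference / SD. For n per group, the noncentrality is λ = d·√(n/2) with 2n − 2 degrees of freedom. Power is the probability that a noncentral t exceeds the two-sided 5% critical value.

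**Step 1: the plan's own figure, nobody lost.**

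- mmol/mol: d = 6/7 = 0.857; λ = 0.857 × √11.5 = 2.907; critical t on 44 df = 2.015; power **0.811**.
- Per cent: d = 0.5/0.6 = 0.833; λ = 0.833 × √11.5 = 2.826; power **0.789**.
- Normal approximation, Φ(λ − 1.96): 0.828 and 0.807.

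None of these reaches 0.85. For 85% by t-test, the required n is 25.4 on the first scale and 26.9 on the second, that is 26 or 27 per group. One-sided tests at 23 per group give 0.87 to 0.90, so a change of sidedness does not explain the figure either.

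**Step 2: the effect of loss.** The numbers lost are assumptions. The last column uses d = 0.9035, the value at which 23 per group gives exactly 85% by t-test.

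| Evaluable per group | Lost | 6 ± 7 mmol/mol | 0.5 ± 0.6% | d = 0.9035 |
|---|---|---|---|---|
| 23 | 0% | 0.811 | 0.789 | 0.850 |
| 22 | 1/23 = 4% | 0.793 | 0.770 | 0.833 |
| 21 | 2/23 = 9% | 0.773 | 0.750 | 0.815 |
| 20 | 3/23 = 13% | 0.752 | 0.728 | 0.795 |
| 18 | 5/23 = 22% | 0.705 | 0.680 | 0.750 |

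Loss from one arm only costs about the same: 23 against 19 gives 0.770 and 0.746.

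**Step 3: separating the two parts.** At 21 per group on 6 ± 7, the gap from 0.85 is 7.7 points. Of this, 0.850 − 0.811 = 3.9 points is the calculation not reproducing, and 0.811 − 0.773 = 3.8 points is loss.

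**Step 4: the composite.** Rates are 10% and 50%, mean 0.30. With n = 20, power = Φ[(0.40 − 1.96·√(2·0.30·0.70/20)) / √((0.10·0.90 + 0.50·0.50)/20)] = Φ[(0.400 − 0.284)/0.130] = 0.813. The stated 0.80 reproduces. With n = 23 the same formula gives 0.867, so three per group can be lost before the planned 20 is reached. This is for the uncorrected chi-square test. With a continuity correction the formula asks for 25 per group, and the article does not say which version is meant.

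**The case against.** The strongest reply has four parts.

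1. **Rounding could explain the 85%.** d = 0.9035 corresponds to an SD of 6/0.9035 = 6.64 mmol/mol, which prints as 7, or 0.5/0.9035 = 0.55%, which prints as 0.6. The original inputs may therefore have given 85%. This is possible but not shown. It affects only the starting point, because the last column of the table still falls with each loss.
2. **The article forecasts no attrition.** Imputation as a sensitivity analysis is routine provision, and section 2.3 does not call its 23 evaluable. This stands: the plan provides for missing values without predicting any, and the losses above are illustrations.
3. **How the primary t-test handles a missing value may be set in a document not shown.** This also stands as a caution. The article does place imputation under sensitivity analyses and names none for the primary test.
4. **Enrolment is complete and the correction changes no analysis.** True, but the stated power is the yardstick for reading a negative result.

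A reader might infer more than this in three ways. One is that 46 is exactly what the HbA1c calculation needs, so that 85% holds as long as nobody is lost. The printed inputs do not support that, since they give 0.79 to 0.81 at zero loss. A second is that both primary outcomes are sized too small. The composite needs only 20 per group on its own stated figures, and its exposure comes through the gate. A third is that the article fails to keep participants who stop fasting in follow-up. A condensed article commonly leaves that to the full protocol, so it is not a finding here.

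**Conclusion.** The point holds for HbA1c. The number randomised equals the number calculated, with no margin for loss, and the stated 85% is not what the printed inputs deliver. The shortfall is about 4 points (mmol/mol) or 6 points (per cent) with complete follow-up. Two losses per group add about 4 points and three add about 6. If d is taken as about 0.90 so that 85% is right at 23 per group, only the loss part remains, and power is 0.815 at 21 and 0.795 at 20.

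This rests on two assumptions: that a participant without a week-12 HbA1c does not enter the primary t-test, and that the loss is of the illustrated size. The step from 85% to 0.79–0.81 needs neither. The composite keeps its own planned power with up to three lost per group, under the uncorrected test, but cannot be claimed unless HbA1c is significant.

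**What to change.** In section 2.3:

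- Replace 85% with the power that 23 per group gives on the stated inputs, about 0.79 to 0.81. If unrounded inputs were used, print them with the power they give.
- Say that this figure assumes a week-12 HbA1c in every participant.
- Add the power for plausible evaluable numbers, for example 0.77/0.75 at 21 per group and 0.75/0.73 at 20.

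The cost is a change of wording and a less favourable stated power. Neither enrolment nor the analysis changes.

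### The 85% power for HbA1c is not reproduced by the inputs as printed (about 81% or 79% with 23 per group); give the unrounded inputs or restate the power

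*Protocol article*

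**What the plan says.** Section 2.3 of the protocol article claims that "a sample size of 23 participants in each group will have a power of 85% to detect a clinically important mean difference". The effect is given in two units, as a "mean difference of 6 ± 7 mmol/mol (0.5 ± 0.6%) in HbA1c between the groups", with a two-sided 5% alpha. On where the inputs come from, it says: "We based our sample size estimation on the baseline HbA1c data of this study". That baseline value is 66 ± 7 mmol/mol (8.2 ± 0.6%), so the SD attached to the between-group difference is the same number as the baseline SD of the cited trial.

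Section 2.8.19 names the primary analysis of the first primary outcome: an unpaired t-test on the change in HbA1c from baseline to week 12, in all randomized participants. Multiple imputation is listed as a sensitivity analysis, and adjustment for baseline HbA1c as a further analysis. The composite outcome is tested only if the HbA1c test is significant.

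The text with Figure 1 gives the number randomized: "46 participants (23 per group) with insulin‐treated type 2 diabetes mellitus are randomly assigned". Section 2.8.23 reports that all 46 have been recruited.

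**The concern.** Section 2.3 prints every figure that a power calculation for two means needs, and section 2.8.19 names the test. A reader can therefore repeat the calculation, and neither printed pair returns 85%.

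HbA1c is the first test in the hierarchy, so its power also governs how often the composite is formally tested. If the result is not significant, readers will set it against a claimed 15% chance of missing the target difference. On the printed inputs that chance is 19% to 21%.

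Two assumptions behind the figure are also left unsaid. The SD comes from baseline values, while the endpoint is a change. And the calculated 23 per group is also the number randomized, so the stated power presumes a week-12 HbA1c from everyone.

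**Working it through.** **Inputs.** n = 23 per group, two-sided alpha 0.05, difference and SD 6 and 7 mmol/mol or 0.5 and 0.6% (all section 2.3); unpaired t-test (section 2.8.19).

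**1. Attempt to reproduce 85%.** Standardized difference d = difference / SD; noncentrality = d × √(n/2); df = 2n − 2 = 44; critical t = 2.015. The normal approximation is Φ(noncentrality − 1.960).

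| Pair as printed | d | Noncentrality | Power, t-test | Power, normal approximation |
|---|---|---|---|---|
| 6 / 7 mmol/mol | 0.857 | 0.857 × √11.5 = 2.907 | 81.1% | Φ(0.947) = 82.8% |
| 0.5 / 0.6% | 0.833 | 0.833 × √11.5 = 2.826 | 78.9% | Φ(0.866) = 80.7% |

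One-sided 5% tests would give 87% to 90%, but the text says two-sided. None of these is 85%.

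**2. What 85% would require.** With the t-test, the mmol/mol pair needs 26 per group (85.8%) and the percentage pair 27 per group (85.2%). With 23 per group, d must be about 0.903: a difference of 0.903 × 7 = 6.3 mmol/mol at SD 7, or an SD of 6 / 0.903 = 6.6 mmol/mol at a difference of 6.

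**3. Could rounding account for it?** Treat the two pairs as one set of values rounded in two units. Assume about 10.9 mmol/mol per 1%; the article's own pairs, 53 with 7.0% and 66 with 8.2%, imply 13 / 1.2 = 10.8.

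- Difference: printing as 6 needs 5.5 to 6.5 mmol/mol. Printing as 0.5% needs less than 0.55 × 10.9 = 6.0 mmol/mol. Both together: about 5.5 to 6.0.
- SD: printing as 7 needs 6.5 to 7.5 mmol/mol. Printing as 0.6% needs less than 0.65 × 10.9 = 7.1 mmol/mol. Both together: about 6.5 to 7.1.
- Least favourable corner, 5.5 / 7.1: about 73%. Most favourable, 6.0 / 6.5: about 87%.
- A difference of 6.0 with SD 6.6 mmol/mol gives 85.4%. At 10.9 per 1%, 6.0 sits on the rounding boundary, but a value just below it serves as well: 5.97 / 6.6 gives 85.1%.

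So 85% is attainable from values that print as shown, but only with the difference close to its upper limit and the SD close to its lower one.

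**4. SD of the change (sensitivity only).** If 7 mmol/mol is the SD at each time point, SD of change = 7 × √(2(1 − ρ)), where ρ is the baseline to week-12 correlation. This equals 7 only at ρ = 0.5. The article gives no ρ. Over an assumed range, with a difference of 6 and 23 per group:

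| Assumed ρ | SD of change | Power |
|---|---|---|
| 0.3 | 8.28 | 67% |
| 0.5 | 7.00 | 81% |
| 0.55 | 6.64 | 85% |
| 0.7 | 5.42 | 96% |

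**5. Missing week-12 values (illustration only).** The article gives no loss rate. If 20 per group were evaluable, power would be 75% for 6/7 mmol/mol and 73% for 0.5/0.6%.

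**The case against.** The strongest reply is rounding. The inputs are printed to one significant digit in two units, and step 3 shows that values consistent with both pairs can give 85%. This stands. It means that the authors' calculation may have been right, that the different ratios of the two pairs need not be two different effect sizes, and that a flat instruction to print 81% could replace a correct figure with a wrong one. It does not make the printed statement checkable: neither pair as shown yields 85%, and the compatible range extends further below 85% than above it.

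A reader might infer that the trial is underpowered, or that its true power is known to be below 85%. The article does not support that. The SD of the change is not given, and step 4 moves power in either direction; a correlation of 0.55 is enough to restore 85%. Nor does the article give a dropout rate, so 20 evaluable per group is an assumption made here.

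It is also fair to say that the stakes are limited. Even at face value power stays close to 80%, all 46 participants are recruited, and the stated power changes neither the test, the alpha, the hierarchy nor the estimate. A null result will be judged mainly from its confidence interval. The planned imputation, mixed models and baseline adjustment are sensitivity or further analyses, so they do not supply the power claimed for the primary t-test.

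**Conclusion.** The point holds as a failure to reproduce. With 23 per group, two-sided 5% and an unpaired t-test, the printed inputs give 81% or 79% (83% or 81% by normal approximation) against a stated 85%, a shortfall of 4 to 6 percentage points with the planned test. This takes the printed figures at face value and assumes 23 evaluable per group. Rounding is a plausible explanation that the authors can confirm or rule out.

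The baseline origin of the SD and the lack of any allowance for missing values are unstated assumptions that belong in the same paragraph. They do not show by themselves that power is below 85%. Severity is moderate.

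**What to change.** Revise the HbA1c part of section 2.3 as follows.

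- Give the unrounded difference and SD, in one unit, together with the test assumed, if they yield 85% with 23 per group. Otherwise restate the power as about 81% for 6 against SD 7 mmol/mol with 23 evaluable per group.
- Say that 7 mmol/mol is taken from baseline values and used as the SD of the change, which is equivalent to assuming a baseline to week-12 correlation of 0.5.
- Say that 23 per group includes no allowance for missing week-12 HbA1c. A labelled illustration would help: about 75% power with 20 evaluable per group, on the 6/7 mmol/mol inputs.

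The cost is one paragraph of wording and possibly a less favourable power figure. No change to enrolment, test or hierarchy is asked for.
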